### Outcomes

2.5

#### Primary outcome measurement

2.5.1

We will use numeric rating scale (NRS)^[17]^ as the primary outcome for assessing the severity of LBP, by evaluating intensity of low back pain (LBP) on a scale range of 0 (no pain at all) to 10 (worst pain imaginable). The participants will be asked to rate their pain on a defined scale at each assessment. The changes in the pain intensity between the 3 groups will be analyzed.

#### Secondary outcome measurement

2.5.2

Secondary outcome measures include evaluation of the functional disability status using Roland Morris Disability Questionnaire (RMDQ),^[18]^ and overall quality of life (QoL) by European QoL 5 Dimension (EQ-5D).^[19,20]^ An adapted Korean version of RMDQ is a reliable measurement for evaluating disability of daily life and consists of 24 questions representing different aspects of functional disability, which is reflected by high total score in the questionnaire. The representative validated QoL measurement tool, EQ-5D, captures an individual's current health status. It contains 3 levels of severity of daily life discomfort which comprises of 5 dimensions, including mobility, self-care, usual activities, pain/discomfort, and anxiety/depression and quantitative self-reported visual analogue scale. The score will be recalculated by Korean estimated weighted-value model of QoL.

#### Other outcome measurements

2.5.3

Safety outcomes will include physical examination, complete blood count, biochemistry, kidney function test (blood urea nitrogen [BUN] and creatinine), and liver function test (alanine transaminase [ALT], aspartate transaminase [AST], alkaline phosphatase [ALP], and gamma-glutamyl transferase [γ-GT]).^[21]^ Safety will be assessed at screening and visit 6; BUN, creatinine, ALT, AST, and γ-GT will also be assessed at visit 4, and vital signs will be determined at every visit.

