**Figure 1 F1:**
[figure not shown]
Study flow diagram.

After randomization, the participants will receive medication for 4 weeks, and an additional 4 weeks of follow-up, during which they will visit the clinic once every 2 weeks. To manage adherence to the interventional products, study staff will ask participants to return the unused products for calculating compliance at every visit.

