### Withdrawal and dropout

2.4

Subjects may withdraw from the trial for any reason, without penalty. If a subject indicates his/her wish to withdraw, the site PI may clarify the reason of withdrawal and discontinue participation. Termination from the study will be at the discretion of the PI in the event of protocol violations such as prohibited concomitant medications and inadequate compliance. All the progress notes on trial terminations are documented on the case report forms (CRF) with reasons.

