**Table 4 T4:**

Study hypotheses for statistical analysis plan.

Baseline demographic data will be analysed using a *t* test for continuous data and a chi-square test for categorical data. All outcome measures will be calculated as the mean changes between pre- and post-treatments that will be compared using a paired *t* test for intragroup analysis and a Student *t* test for intergroup analysis. Any variables that are to be assessed repeatedly during the trial will be analysed by comparing the mean changes over time using a repeated-measures ANOVA test. Missing data will be using the Last-observation-carried-forward (LOCF) analysis method. There will be no interim analysis for any reason. And we will not establish the data and safety monitoring committee due to the resource and personnel limitations.

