### Harms

2.7

All participants will be informed of potential adverse events (AE) occurring during the trial and prior to enrollment. When AEs occur, the participant may immediately report to the site trial staff. Each AE will be noted in the electronic healthcare record system and CRF by the site trial staff thoroughly and assessed for causality. Serious adverse events (SAEs) will be reported by the site staff to the site principal investigator and the Institutional Review Board (IRB) at the earliest. After receiving an SAE report, the site principal investigator will decide on the continuation of the participant in the trial. If any conditions for compensation to those who suffer harm from trial, we have contracted medical liability insurance for patient safety.

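### LOCF applied to every outcome would enter the screening laboratory value as a zero change for participants who leave before visit 4 (before visit 6 for blood count and ALP)

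*Protocol article*

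**What the plan says.** Laboratory schedule (section 2.5.3, under the Outcomes heading). Physical examination, blood count, biochemistry, kidney function and liver function tests are named as safety outcomes. Their timing is "Safety will be assessed at screening and visit 6". In addition, "BUN, creatinine, ALT, AST, and γ-GT will also be assessed at visit 4". Blood count and ALP are not in that visit 4 list. Outside the laboratory, "vital signs will be determined at every visit".

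Leaving the trial (section 2.4). When a subject wishes to withdraw, "the site PI may clarify the reason of withdrawal and discontinue participation". The investigator may also terminate participation for protocol violations, including poor compliance. What is recorded is stated: "All the progress notes on trial terminations are documented on the case report forms (CRF) with reasons". The section does not mention a laboratory sample, either to require one or to exclude one.

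Analysis (section 2.5.5, text below the Table 4 caption). All outcomes are to be analysed as mean change from before to after treatment, with repeated-measures ANOVA where there are repeated values, in both an intent-to-treat and a per-protocol analysis. Then: "Missing data will be using the Last-observation-carried-forward (LOCF) analysis method". Neither sentence is limited to efficacy.

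Adverse events (section 2.7). "Each AE will be noted in the electronic healthcare record system and CRF by the site trial staff thoroughly and assessed for causality". This collection is not tied to a visit number.

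**The concern.** LOCF is usually debated for efficacy scores, where the carried value is often a post-baseline one. Here the laboratory tests have at most two post-baseline time points, and blood count and ALP have one. For an early leaver the last observation is therefore often the screening sample, taken before any study product. Carrying it forward states that nothing happened to that person's liver, kidney or blood values, although nothing was measured.

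The error would favour the product if people who leave are more likely than others to have an abnormal value. The article does not show that they are, but the possibility is plain enough that an analysis should not assume the opposite. Filled values also hide the missingness: a table with a full denominator does not tell the reader how many participants were never sampled after baseline. The Discussion says that the trial was designed to explore safety as well as efficacy and offers its safety results as a basis for larger trials, so the laboratory summary will be used.

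**Working it through.** The article gives no figure for this point, so there is nothing to reproduce. The check sets the schedule against the missing-data rule and then illustrates the effect.

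**Step 1. What is available to carry forward.** Screening precedes the run-in and randomisation (section 2.2.2), so its value is pre-treatment.

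| Test | Post-baseline samples scheduled | Leaves before visit 4: value carried | Leaves after visit 4, before visit 6: value carried |
|---|---|---|---|
| BUN, creatinine, ALT, AST, γ-GT | visits 4 and 6 | screening (change = 0) | visit 4 value |
| Blood count, ALP | visit 6 only | screening (change = 0) | screening (change = 0) |

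This needs only that visit 4 falls after treatment starts. It does not need the exact week.

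**Step 2. Timing, under an assumption.** The text says "the participants will receive medication for 4 weeks, and an additional 4 weeks of follow-up, during which they will visit the clinic once every 2" (the interval is in weeks), but the flow chart that would match visit numbers to weeks is not shown. If visit 1 is screening and visit 2 is week 0, visits 3, 4, 5 and 6 are weeks 2, 4, 6 and 8. Visit 4 would then be the end of treatment and visit 6 four weeks later. In that case someone who completes treatment but misses visit 6 would still have zero change entered for blood count and ALP.

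**Step 3. Effect on a mean change.** Let m be the share of an arm filled with the screening value, d the mean change among those sampled and d_L the unobserved mean change among those filled.

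- True mean: (1 − m)d + m·d_L
- LOCF mean: (1 − m)d, which falls short by m·d_L
- As-observed mean: d, which falls short by m(d_L − d)

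For assumed m = 5%, 10% and 20%, LOCF reports 0.95d, 0.90d and 0.80d. With 150 participants allocated 1:1:1, an arm has 150/3 = 50 and about 2 × 50 = 100 receive the herbal product. The three values of m are then 5, 10 and 20 of those 100.

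**Step 4. Effect on an abnormality rate.** Assume a true rate t = 5%, normal screening values, 10% of unaffected participants leaving before visit 4, and a share L of affected participants leaving before visit 4. Under LOCF the reported rate is t(1 − L), because leavers count as normal in a full denominator. As observed it is t(1 − L)/[t(1 − L) + (1 − t)(0.9)].

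| L | LOCF | As observed |
|---|---|---|
| 10% | 4.5% | 5.0% |
| 30% | 3.5% | 3.9% |
| 50% | 2.5% | 2.8% |
| 80% | 1.0% | 1.2% |

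For L = 50%: LOCF 0.05 × 0.5 = 0.025; as observed 0.025/(0.025 + 0.855) = 0.028. LOCF is lower in every row, but most of the shortfall when L is large comes from the missing samples themselves.

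**Step 5. Chance of seeing any case.** This depends on sampling, not on imputation: 1 − [1 − t(1 − L)]^n. For n = 100 and an assumed t = 2%, it is 0.87 with no loss, 0.63 if half of those affected leave before visit 4 and 0.33 if 80% do. These figures bear on whether samples are taken at early exit, which the article does not settle.

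**The case against.** The strongest objection is that this is a condensed article. The full protocol (version 1.3) and any analysis plan are not shown, and they may exempt safety data from LOCF. The LOCF sentence follows text on t tests and ANOVA, and the article never says in so many words that laboratory values will be imputed. Some implementations of LOCF also carry forward only post-baseline values. This lowers confidence about what will be done. It does not change what the article states: one missing-data rule, without limits, for outcomes that include the laboratory tests. An intent-to-treat analysis that keeps a participant who has no later sample would have only the screening value to use.

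A reader might infer more: that no assessment is made when a participant leaves early, and that the whole safety result therefore rests on those who tolerated treatment. The documents support neither. Section 2.4 is silent on exit samples, and silence in an article on a detail commonly left to the full protocol is not evidence that none are taken. Section 2.7 has every adverse event recorded and assessed for causality, and vital signs are taken at each visit. A participant who stops because of feeling unwell is someone that this reporting is meant to capture. Those who leave after visit 4 also have the renal and hepatic subset.

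It is also fair to say that the trial is a pilot, that the number of early leavers may be small, and that nothing in the document links laboratory abnormality to leaving. These points limit the size of the problem but give no reason to keep the imputation.

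**Conclusion.** The concern holds in a limited form. As written, the LOCF rule in section 2.5.5 reaches the laboratory outcomes of section 2.5.3 and turns absent post-baseline values into zero changes: before visit 4 for the renal and hepatic subset, and before visit 6 for blood count and ALP. The bias is towards no change and affects the laboratory summary only.

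Its size cannot be derived, because section 2.5.4 mentions expected attrition without a figure and no toxicity rate is given. All rates, shares and detection probabilities in the working are illustrations under assumed inputs. Analysing the data as observed removes the invented zeros and makes the missingness visible. It does not remove selection if leaving is related to toxicity. Whether samples are taken at early exit is a point to confirm, not an error shown by the article.

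**What to change.** In section 2.5.5, restrict LOCF to the efficacy outcomes. State that laboratory safety data are analysed as observed, that a post-baseline value is never filled with the screening value, and that the number of participants without any post-baseline sample is reported by arm. Give that number separately for the visit 4 subset and for blood count and ALP, since their schedules differ.

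The sponsor should also check the full protocol and state in section 2.4 or 2.5.3 whether the panel already listed is requested at early exit.

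The analysis change is a few sentences and needs no extra blood draw or visit. The confirmation costs a look at the full protocol.

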#### Sample size

2.5.4

This is a pilot study to explore the efficacy of single or multiple therapies using SGHH and Chuna, feasibility of the study design and effect size for further large-scale studies. A sample size of 150 patients, which is not estimated based on previous studies, was considered after assessing their LBP clinic visit rates, skilled labor availability, budget, and expected attrition at each site.

#### Statistical management

2.5.5

An independent statistician from ISEE who is blinded to the treatment allocation will conduct data analysis by both intent-to-treat (ITT) and per-protocol (PP) analysis. The data analysis strategy for testing each study hypotheses is summarized in Table 4.

**Table 4 T4:**

Study hypotheses for statistical analysis plan.

Baseline demographic data will be analysed using a *t* test for continuous data and a chi-square test for categorical data. All outcome measures will be calculated as the mean changes between pre- and post-treatments that will be compared using a paired *t* test for intragroup analysis and a Student *t* test for intergroup analysis. Any variables that are to be assessed repeatedly during the trial will be analysed by comparing the mean changes over time using a repeated-measures ANOVA test. Missing data will be using the Last-observation-carried-forward (LOCF) analysis method. There will be no interim analysis for any reason. And we will not establish the data and safety monitoring committee due to the resource and personnel limitations.

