#### Randomization

2.2.2

The flow chart describing the trial protocol is shown in Fig. 1. The study population will enroll 150 eligible participants who will undergo a 7-day run-in period prior to randomization. The participants will be randomly allocated to the SGHH group, SGHH with Chuna group or placebo with Chuna group at a ratio of 1:1:1. Random allocation will be facilitated by a web-based application designed by the contract research organization (CRO), the Institute of Safety and Effectiveness Evaluation for Korean Medicine (ISEE), Kyung Hee University. Independent staff from ISEE will use the SAS 6.1 program for randomization list generation and stratification of the trial sites using block sizes of 3 or 6. Once the participant is randomly assigned to a group, patients will not be informed of the type of allocation that they will receive. However, due to diverse intervention strategies, this trial is designed as an assessor- and analyst-blinded study. Participants will be cautioned on confidentiality of allocation prior to outcome assessment and an independent assessor will evaluate allocation in a secured area without seeking information on treatment allocation that the participant will receive. The final dataset will be sent to data analysts without information on treatment allocations to avoid bias in the analysis of study results. In case of expected abnormal symptoms or occurrence of urgent medical conditions, the site's PI will directly inform ISEE and the sponsor to unblind the treatment allocation according to the standard operating procedures (SOPs).

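### The rule that every outcome is compared as a mean change also covers the laboratory safety tests, where it is nearly blind to one to three affected participants per arm

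*Protocol article*

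**What the plan says.** Section 2.5.3 (Other outcome measurements) classes the laboratory tests as outcomes: "Safety outcomes will include physical examination, complete blood count, biochemistry, kidney function test", followed by the liver enzymes. On timing it says: "Safety will be assessed at screening and visit 6; BUN, creatinine, ALT, AST, and γ-GT will also be assessed at visit 4".

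Section 2.5.5 (Statistical management, text under the Table 4 caption) then sets a single rule: "All outcome measures will be calculated as the mean changes between pre- and post-treatments", to be "compared using a paired *t* test for intragroup analysis and a Student *t* test for intergroup analysis". Variables assessed repeatedly are to be "analysed by comparing the mean changes over time using a repeated-measures ANOVA test". Missing data are handled by LOCF. None of these sentences makes an exception for safety outcomes.

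Two other places bear on the point. Section 2.7 (Harms) has each adverse event recorded and assessed for causality, with serious events reported to the site principal investigator and the ethics board. Section 3 (Discussion) promises preliminary safety results, as well as efficacy results, for later large trials.

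**The concern.** Liver and kidney tests are taken in a herbal-medicine trial mainly to find the few participants who react badly, not to estimate a small average shift in everyone. A comparison of means answers the second question. A few very high values move the group mean only slightly and inflate the standard deviation at the same time, so the t statistic stays small.

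LOCF works in the same direction. Where screening is the only value available, carrying it forward enters a change of exactly zero, including for someone who left because of harm.

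What is at stake is the use made of the laboratory data. The only analysis that the article states for them would show little if a few participants in one arm had marked abnormalities, yet the trial is meant to inform the safety side of larger studies.

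**Working it through.** **Inputs from the article**
- "The study population will enroll 150 eligible participants", allocated to "SGHH group, SGHH with Chuna group or placebo with Chuna group at a ratio of 1:1:1" (2.2.2), so 150 / 3 = 50 per arm.
- No power calculation exists to reproduce: "A sample size of 150 patients, which is not estimated based on previous studies" (2.5.4).
- ALT, AST, γ-GT, BUN and creatinine are measured at screening, visit 4 and visit 6. The other tests, such as ALP and the blood count, are measured at screening and visit 6 only (2.5.3).

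**Step 1. A limit that needs no assumed standard deviation.** Let k of n = 50 participants in one arm have the same rise R, and let everyone else in both arms have no change.
- Difference in means = kR/n.
- Sample variance in the affected arm = kR²(n − k) / [n(n − 1)]; it is zero in the other arm.
- Standard error = R √{k(n − k) / [n²(n − 1)]}.
- The ratio is t = √[k(n − 1)/(n − k)] = √[49k/(50 − k)].

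R cancels. This is the value that t approaches as the rises become large relative to ordinary variation. With 98 degrees of freedom, the two-sided 5% critical value is 1.98.

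| k of 50 v 0 of 50 | limiting t | p |
|---|---|---|
| 1 | √(49/49) = 1.00 | 0.32 |
| 2 | √(98/48) = 1.43 | 0.16 |
| 3 | √(147/47) = 1.77 | 0.08 |
| 4 | √(196/46) = 2.06 | 0.04 |

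**Step 2. Finite rises with ordinary variation.** The article gives no ALT figures, so these inputs are assumptions: two-sided alpha 0.05, normally distributed change with SD 6, 10 or 15 U/L, and a rise of 100 or 200 U/L in each affected participant. The table gives the share of 20,000 simulated trials (50 v 50, Student t test) with p < 0.05, as a range over those settings.

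| Affected in one arm | p < 0.05 |
|---|---|
| 1 | 0% to 5% |
| 2 | 0.2% to 9% |
| 3 | 8% to 19% |
| 5 | 45% to 99% |

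One rise of 100 U/L moves the arm mean by 100/50 = 2 U/L. With one or two cases, the larger rise was detected less often than the smaller one at every SD tried.

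**Step 3. Repeated-measures ANOVA.** The five tests also taken at visit 4 fall under this sentence as well. It still compares mean changes, so it does not escape the problem.

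**Step 4. LOCF.** For ALP and the blood count, a participant who leaves before visit 6 without a further test has only the screening value. Carried forward, the change is screening − screening = 0. For the five tests with a visit 4 value, anyone leaving between visits 4 and 6 keeps the visit 4 value, so a later rise is not seen.

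**Step 5. What counting would and would not give.** Fisher's exact test for k of 50 v 0 of 50 gives p = 1.00, 0.49, 0.24, 0.12 and 0.056 for k = 1 to 5. Counting is therefore not a more powerful test. What it gives is a visible number and an interval:
- 0 of 50: one-sided 95% upper limit 1 − 0.05^(1/50) = 5.8%; upper end of a two-sided exact 95% interval 1 − 0.025^(1/50) = 7.1%.
- 0 of 100 (both SGHH arms together): one-sided 95% upper limit 1 − 0.05^(1/100) = 3.0%.

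**The case against.** The strongest reply is that the sentence in 2.5.5 was probably written for the efficacy scales. Physical examination, the first safety outcome listed in 2.5.3, normally has no mean change, so the literal scope cannot have been fully intended. That is plausible, but it supports correcting the scope and does not make the wording right.

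A second reply is that shift tables, case listings and analysis populations for safety commonly belong in the full protocol or analysis plan, which are not shown. This stands: their absence from an article is no finding. The finding is that the stated rule reaches outcomes for which it is unsuitable.

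Two stronger readings are tempting and should not be drawn.
- A reader might infer that the trial would miss individual liver or kidney injury. Section 2.7 records each adverse event and its causality participant by participant, so harm has its own channel. That section does not say when an abnormal laboratory value becomes an adverse event, so it does not replace the group analysis.
- A reader might infer that the trial plans to declare no safety difference from a non-significant test. No section says so. It is a possible misuse, not a stated plan.

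The insensitivity also has a bound. At four cases the limiting t passes the critical value, and at five the simulated detection rate is 45% or more.

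**Conclusion.** The point holds for the group-level laboratory safety analysis. As worded, 2.5.5 sends the tests of 2.5.3 to a comparison of means that is nearly blind to one to three markedly abnormal participants among 50 (up to 6% of an arm), and its LOCF rule can enter zero change where nothing was measured.

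The limiting t values depend only on 50 per arm, equal rises in the affected participants and none in the other arm. The simulated percentages also depend on the assumed SDs and rises. Dropout would make the arms smaller than 50.

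The size is minor to moderate. This is a self-described pilot, adverse events are captured separately, and the fault is one over-broad rule.

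**What to change.** In 2.5.5:

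1. Limit the mean-change, t-test, repeated-measures ANOVA and LOCF sentences to the efficacy outcomes NRS, RMDQ and EQ-5D.
2. Summarise laboratory safety per arm as the number and proportion of participants with an out-of-range or worsened value at any post-baseline visit, from observed data without carrying values forward, with exact 95% intervals.
3. State that a non-significant difference in means is not evidence of safety.

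The cost is a few sentences and one or two tables from data already being collected. No extra visits, tests or participants are needed. The gain is that cases become visible and the uncertainty is stated honestly: even no cases in 50 remains compatible with a true rate of about 6% (one-sided 95%).

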### Study setting

2.1

This study will be a multicenter, assessor- and analyst-blinded, incomplete factorial, randomized, parallel group, placebo-controlled clinical trial. Four university-affiliated TKM hospitals and one private secondary care hospital are chosen to be the study sites – Gil Oriental Medical Hospital of Gachon University, Semyung University Second Affiliated Oriental Medical Hospital at Jecheon, Dunsan Korean Medicine Hospital of Daejeon University Woosuk University of Korean Medicine and the Jaseng Hospital of Korean Medicine. Recruitment will be facilitated using hospital on/offline bulletin boards, and local community-based newspaper advertisements.

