## Discussion

3

cnLBP affects daily activity and QoL but despite multiple treatment strategies in clinical practice, they have not been systematically evaluated. This protocol was designed to explore the safety and efficacy of SGHH and CMT in patients with cnLBP based on an incomplete factorial design. To the best of our knowledge, this is the first study to evaluate the safety and efficacy of mono- and multiple herbal therapies and CMT on cnLBP.

This study design is not without challenges. First, the results may fail to reach a conclusive conclusion due to the small sample size. Second, incomplete factorial design with naïve comparison may impact the generalizability of the results. Despite these limitations, this will be the first well-planned RCT to investigate the efficacy of SGHH and CMT in cnLBP patients. The findings from this study will provide preliminary efficacy and safety results for future head to head, large-scale RCTs. During the progress of trial, any potential biases that may affect the trial results will be minimized.

Nevertheless, this trial will provide valuable information, such as study design, outcome variables, pain characteristics associated with each occupation, and statistical power for sample size calculation for future large-scale trials and the future development of general clinical guidelines for cnLBP in the field of Korean medicine.

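### The between-group test on change scores fixes the baseline coefficient at 1 and leaves out the site strata; adjusting for baseline and site costs nothing and gains from almost no precision to about a third of the variance

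*Protocol article*

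**What the plan says.** Section 2.5.5 (Statistical management) fixes the outcome metric: "All outcome measures will be calculated as the mean changes between pre- and post-treatments". It names a paired t test within groups and a Student t test between groups. Variables measured repeatedly also get a repeated-measures ANOVA of mean changes over time. No baseline covariate or site term is named for either between-group method. Section 2.5.1 describes the primary analysis of the 0 to 10 pain NRS in the same terms: "The changes in the pain intensity between the 3 groups will be analyzed".

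Section 2.2.2 (Randomization) describes "randomization list generation and stratification of the trial sites using block sizes of 3 or 6", and section 2.1 gives five strata: "Four university-affiliated TKM hospitals and one private secondary care hospital are chosen to be the study sites".

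On size, section 2.5.4 states "A sample size of 150 patients, which is not estimated based on previous studies". It calls the trial a pilot and lists an effect size for later trials among its aims. The Discussion concedes that "the results may fail to reach a conclusive conclusion due to the small sample size".

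**The concern.** A two-sample t test on change makes two choices that the design does not require.

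- It subtracts the whole baseline value from the follow-up value, so the slope of follow-up on baseline is taken to be 1. If the true slope is below 1, as it commonly is for a noisy pain score, the subtraction over-corrects. The baseline noise adds to the error, and a chance baseline difference between arms carries into the estimate with the opposite sign.
- It drops the factor on which the randomisation was balanced, so the analysis does not match the allocation scheme.

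At stake is the precision of the treatment contrast. The sample size was set by feasibility and the authors expect that it may not be conclusive, so an efficient analysis is one of the few levers left. The estimate is also meant to inform later trials, so avoidable noise or an imbalance-driven shift would pass into their sample-size planning.

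**Working it through.** **Inputs from the article.** 150 participants, allocated to the "SGHH group, SGHH with Chuna group or placebo with Chuna group at a ratio of 1:1:1". That is 150/3 = 50 per arm and 100 per pairwise comparison, before attrition. There are five sites. The article reports no power or detectable difference, so there is no figure of that kind to reproduce.

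**Assumed, because the article does not give them.** Baseline to follow-up correlation r of 0.3 to 0.7; baseline SD sx and follow-up SD sy in NRS points; two-sided 5% level.

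**Step 1: precision.** Per participant,

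- Var(change) = sx² + sy² − 2·r·sx·sy
- Var(ANCOVA) = sy²(1 − r²)
- difference = (sx − r·sy)², which is never negative.

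The two are equal only when the slope β = r·sy/sx is exactly 1. With sx = sy the ratio ANCOVA/change reduces to (1 + r)/2.

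| r | Ratio, equal SDs | Ratio, sx = 1.5 and sy = 2.0 |
|---|---|---|
| 0.3 | 0.65 | 3.64/4.45 = 0.82 |
| 0.5 | 0.75 | 3.00/3.25 = 0.92 |
| 0.7 | 0.85 | 2.04/2.05 = 0.995 |

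To match ANCOVA with 50 per arm under equal SDs, the t test on change would need 50/0.65 = 77, 50/0.75 = 67 or 50/0.85 = 59 per arm. With the narrower baseline SD it would need about 61, 54 or 50. A baseline SD wider than the follow-up SD would make the gain larger than in the equal-SD column.

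**Step 2: the same in NRS points.** At 50 per arm, the difference detectable with 80% power is 0.566 residual SDs.

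- sx = sy = 2, r = 0.5: the SD is 2.00 for change and 1.73 for ANCOVA, so the detectable difference is 1.13 against 0.98 points.
- sx = 1.5, sy = 2, r = 0.5: the SD is √3.25 = 1.80 against 1.73, so 1.02 against 0.98 points.

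The protocol sets no power target; this only expresses the variance ratio on the pain scale.

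**Step 3: chance baseline imbalance.** Given a baseline difference D between arms, the change-score contrast is displaced by (β − 1)·D, whereas ANCOVA is not displaced under a linear relation.

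- sx = sy = 2, r = 0.5: β = 0.5. The SE of D is 2·√(2/50) = 0.4, so a two-SE imbalance is 0.8 points and the displacement is 0.4 points.
- sx = 1.5, sy = 2, r = 0.5: β = 0.67. The SE of D is 0.3, so a two-SE imbalance is 0.6 points and the displacement is 0.2 points.

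**Step 4: site.** A site difference present equally before and after treatment cancels in the change score. Only differences between sites in the amount of change stay in the error term. A simulation tested that part: 4,000 runs per setting, five equal sites, 50 against 50, equal SDs, and a site effect placed on follow-up only, at 0 to 10% of the residual variance. ANCOVA with baseline and site gave variance ratios of 0.61 to 0.66 (r = 0.3), 0.73 to 0.76 (r = 0.5) and 0.84 to 0.87 (r = 0.7). These lie close to the baseline-only values of 0.65, 0.75 and 0.85. Type I error was 4.3 to 5.4% for the t test and 4.8 to 5.5% for ANCOVA, against a simulation error of √(0.05 × 0.95/4000) = 0.3 percentage points. The adjusted model has 93 residual degrees of freedom against 98, a trivial cost.

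**The case against.** - **The test is valid.** Over repeated randomisations the t test on change is unbiased and controls type I error. A reader might infer that the planned analysis is biased or that its p values cannot be trusted. The article does not support that; the displacement in step 3 is conditional on the imbalance that happens to occur. This objection stands and limits the point to efficiency and conditional bias.
- **Baseline is used.** It would be wrong to say that the analysis ignores baseline pain. It uses baseline with a fixed coefficient. What stands is that the coefficient is imposed and not estimated.
- **The size is unknown.** The ratio (1 + r)/2 needs equal SDs. The body of the eligibility table is not in the available text, so a pain threshold at entry that narrows the baseline spread cannot be ruled out. With SDs of 1.5 and 2.0 and r = 0.7 the gain all but vanishes. A reader who takes the equal-SD figures as the trial's loss goes further than the article allows.
- **Site matters little for precision.** One might infer that omitting site materially inflates the standard error. Stable site differences cancel, and the simulation shows only a small effect.
- **It is a pilot, and part of the plan is unseen.** No power is claimed, so none is missed. The body of Table 4 is not shown, and covariates are often left to an analysis plan. But the running text names a test that has no room for covariates, so this is a stated choice and not a gap. The pilot's aim of estimating an effect size makes precision more relevant, not less.

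**Conclusion.** The point holds as a recommendation to improve efficiency; it does not show that the planned analysis is invalid. The article commits to an unadjusted comparison of change scores and leaves out the factor used to stratify randomisation. ANCOVA is at least as precise for any r and any pair of SDs, apart from the few degrees of freedom spent, and it protects the estimate against chance baseline imbalance. Over r = 0.3 to 0.7, the variance reduction is 15 to 35% with equal SDs and 0.5 to 18% with SDs of 1.5 and 2.0. Both the correlation and the SDs are assumptions. Nearly all of the gain comes from the baseline term. The case for the site term is consistency with the randomisation, with little extra precision unless sites differ strongly in how much patients change.

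**What to change.** In section 2.5.5, make the main between-group analysis an ANCOVA of end-of-treatment NRS on treatment group, pre-randomisation baseline NRS and site, or the corresponding contrast from a mixed model with the same terms. Report the adjusted mean difference with its 95% confidence interval. Treat RMDQ and EQ-5D in the same way, each with its own baseline. Keep the Student t test on change as a supportive analysis at most. If the repeated-measures ANOVA is retained, state its baseline and site terms.

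The cost is a sentence or two of analysis wording, fixed before the analyst sees allocation. Site is known for every participant and the pre-treatment value is already needed for the change score, so no further patients, visits or data are required.
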